### Secondary outcome measures

(a) Disability of the Arm, Shoulder and Hand (DASH). Functional status will be measured by the DASH questionnaire at every follow up (Figure 2.)

(b) Short Form 36 (SF-36). Quality of Life will be determined, using the SF-36 questionnaire according to the schedule in Figure 2.

(c) Patient estimation of pain and patient satisfaction. Overall satisfaction with the current condition will be determined by the patient, using a visual analog scale (VAS). Patients are asked to set a vertical mark on the VAS for question 1: How would you estimate the pain in the injured hand, ranging from 'No Pain' to 'Worst possible Pain'?; and question 2: How would you estimate your satisfaction with your current condition ranging from 'very satisfying' to 'absolutely unacceptable'?

(d) Patient overall satisfaction with treatment will be determined by the patient, using a 6-step scale ranging from 'very good' to 'non-satisfactory'.

(e) Range of Motion (ROM) of the wrist will be measured with a goniometer at all follow-up examinations by an independent investigator.

(f) Grip strength will be measured with a Jamar dynamometer, comparing the injured to the non-injured wrist and adjusting for dominance.

(g) Radiological healing

(h) Complication rate

### Hypothesis

Those patients suffering an acute complete fracture of the mid third of the scaphoid bone without any dislocation or comminution visible on the CT-scan who are treated surgically with cannulated screw fixation will return to their previous activity level sooner than patients treated non-operatively with short arm cast immobilization.

### Null hypothesis

There will be no difference in terms of return to previous activity level between patients suffering an acute complete fracture of the mid third of the scaphoid bone, without any dislocation or comminution visible on the CT-scan who are treated surgically with cannulated screw fixation and patients treated non-operatively with short arm cast immobilization.

### Sample size calculation

Given what was reported in 2 recent RCTs, it is anticipated that we will detect a significant difference in mean time to return to previous activity level comparing the two groups. However, the primary outcome in these RCTs was return to work, defined as 'time on sick leave' [22] and 'return to full military duty' [12], respectively; who determined the outcome was not defined, nor was the level of posttraumatic physical activity compared with the level prior to the trauma. The 'return to previous activity level' is assumed to be equivalent to the definition of RTW found in the 2 RCTs, but more objective.

According to a survey in the clinics being invited to participate, it can be expected that the odds of patients receiving non operative treatment in relation to those receiving surgery is 1:4 (i.e. there will be 1 patient with short arm cast treatment for each group of 4 patients being operated on).

The sample size calculation for the primary outcome (1) is based on a two-sided two-sample t-test, a significance level of 0.05 and a power of 90%. A difference of 4 weeks between the two groups is likely and a standard deviation of 5 weeks is anticipated. As a 25% loss to follow-up is expected, we recommend a minimum of 112 patients in the cannulated screw group and 28 patients in the short arm cast group.

The sample size calculation for the primary outcome (2) is based on the numbers shown in Table 3: If the sample size in group A is 86 and the sample size in group 2 is 30, the log-rank test for equality of survival curves with a 0.050 two-sided significance level will have a power of approximately 92% to detect the difference between the survival curves specified in the side table.

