## Background

Acute scaphoid fractures mainly occur in active adults, many of whom work as laborers or are involved in competitive athletics; therefore, returning to work or sport is an important goal of treatment. They are the most common fractures of the carpal bones. Time to union of acute scaphoid fractures ranges from 6 to 18 weeks depending on fracture type, localization of the fracture, degree of displacement, and additional soft tissue injury [1-4].

Cast immobilization remains the standard treatment despite the fact that about 20% of fractures fail to heal with conservative treatment[1,5,6]. It is well documented that the rate of nonunion of acute scaphoid fractures is higher for proximal and dislocated fracture types [7-10]. In displaced scaphoid fractures, the nonunion rate rises up to 46%. Advances in the technique and in implants developed for the operative fixation of acute scaphoid fractures have made it technically easier with a higher rate of union [5,11-16]. Operative treatment is recommended for all displaced, unstable and complex fracture types [2,5,13-15,17-20]. In non-displaced acute scaphoid fractures treated by limited access and screw fixation the union rate has been reported as high as 100% [4,5,11-14,21].

The adequate treatment of non-displaced acute scaphoid fractures is still under discussion. A few prospective studies with a limited number of patients and imprecise definitions of fracture type and union were published in 2000 and 2001 [11,12,16]. Despite favoring screw fixation, two recent randomized controlled trials (RCTs) that used 'return to work' (RTW) as an outcome [12,22] did not provide a clear definition or did not define who determined return to work. Neither study administered a patient-derived quality of life measure specific to the wrist like the Disability of the Arm, Shoulder and Hand (DASH) questionnaire [23-25]. In the Cochrane library, there are no systematic reviews or meta-analyses on the treatment of acute scaphoid fractures. Considering the problems associated with prolonged cast immobilization, the complications of non-operative fracture treatment and social/economic factors, it seems appropriate to evaluate the possible advantages of routine operative treatment with a less invasive screw fixation technique for non-displaced acute scaphoid fractures.

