### Primary outcome measures

(1) Questionnaire on physical loading of the wrist in daily life (PLDL-wrist). The PLDL-wrist (Additional file 1: German version, Additional file 2: English translation) is a newly developed 17-item questionnaire, based on the German translation of the DMQ [32]. Each of the items can be answered by either 'YES' or 'NO', leading to a maximum score of 17. At baseline all patients will be interviewed to get the baseline PLDL-score of the last week before the injury. t_0_, being defined as the day of onset of treatment, will be given the baseline PLDL-score. The questionnaire will be repeated at several follow-ups according to the schedule in Figure 2. The individual score at every interview will be expressed as a percentage of the baseline score (PLDL_xweeks_/PLDL_Baseline _* 100) and plotted over time. The endpoint is defined as 'Time to reach the individual 80%-threshold'. To determine the time point at which the 80%-threshold is reached, the change between the first score value exceeding the 80%-threshold and the prior score value is linearized. The intercept of this line and the 80%-threshold represents the linear estimation of the first day of return to previous activity level (t_return_).

(2) Questionnaire on the activity status (QAS). The QAS differentiates between the categories (A) return to work [full; partly; no; not applicable], (B) return to household duties [full, partly, no] and (C) return to leisure activities [full, partly, no]. Using the QAS will allow us to include patients who are not formally employed (e.g. students, housewives and -men, self- or unemployed). At baseline all patients will be asked for their activity status in the last week before the injury. This will be repeated according to the schedule in Figure 2. A patient has returned to previous activity level either when he or she has returned to full work **and** returned to full household duties or – for those not being employed – has returned to full household duties only. Rates of return to previous activity level will be calculated for each of the follow-up periods. Leisure activities are not included in this definition; these are evaluated as secondary outcomes, however.

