### Data analysis

All data analysis for the primary outcomes will be done on an intention to treat basis. As the baseline variables shown in Table 4 are known a priori to be associated with either of the two primary outcomes, they will be collected to ensure we adequately control for their potential confounding effects. In the secondary analysis, the outcomes will be adjusted for these confounding factors.

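### Primary outcome (1), a time-to-threshold endpoint with fixed follow-up, is sized on mean times, and patients who do not reach 80% have no defined value

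*Protocol article*

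**What the plan says.** - **Endpoint** (Primary outcome measures, item 1): "The endpoint is defined as 'Time to reach the individual 80%-threshold". To find that time, "the change between the first score value exceeding the 80%-threshold and the prior score value is linearized", and the return time is read off where the line crosses 80%.
- **Follow-up** (Methods/Design): visits at 6 weeks, 3 months and 6 months, with telephone interviews at 3, 9 and 15 weeks. Nothing is planned after 6 months.
- **Sizing of primary outcome (1)** (Sample size calculation): the calculation "is based on a two-sided two-sample t-test, a significance level of 0.05 and a power of 90" percent. The target is a mean: "it is anticipated that we will detect a significant difference in mean time to return to previous activity level comparing the two groups". The inputs are "A difference of 4 weeks between the two groups is likely and a standard deviation of 5 weeks is anticipated". An expected 25% loss leads to 112 screw and 28 cast patients.
- **Sizing of primary outcome (2)** (same section): a log-rank test on survival curves, 86 against 30 patients, power about 92%. Under Primary outcome measures the planned summary of this outcome is "Rates of return to previous activity level will be calculated for each of the follow-up periods".
- **Analysis** (Data analysis): "All data analysis for the primary outcomes will be done on an intention to treat basis". No test is named for either primary outcome.

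**The concern.** The return time exists only once a score above 80% has been observed. A comparison of means needs a number for every patient, and the article gives neither a value nor a censoring rule for those without one. Followed as written, the comparison keeps patients according to their outcome: those still limited at 6 months disappear, as do those who leave before crossing. The arm with more non-attainers then looks faster than it was. The intention-to-treat promise is not met for these patients, and their partial follow-up is wasted.

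The plan is also uneven. Both primary outcomes measure return to previous activity, but only the second is sized with a method that can accommodate patients who have not returned.

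**Working it through.** **1. Reproduce the plan's figure.** Inputs from Sample size calculation: difference 4 weeks, SD 5 weeks, two-sided 0.05, power 90%, one cast patient to four surgical.

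- Cast n = (1 + 1/4) × (1.960 + 1.282)² × 5² / 4² = 1.25 × 10.51 × 1.5625 = 20.5, so 21 cast and 84 surgical.
- Dividing by 0.75 gives 28 and 112, an exact match.
- Noncentral-t power at 84/21 is 90.1%.

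The arithmetic is right. The 25% loss is met only by inflating N, so the power calculation counts lost patients as contributing nothing.

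**2. Expected losses.** 0.25 × 112 = 28 surgical and 0.25 × 28 = 7 cast. The plan uses one loss rate for both arms.

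**3. Non-attainers if times follow the plan's SD.** The documents give no mean times, so the cast mean is assumed. With a normal distribution, SD 5 and 6 months taken as 26 weeks, the share beyond follow-up is 1 − Φ((26 − mean)/5). The surgical mean is set 4 weeks lower.

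| Assumed cast mean (weeks) | Cast beyond 26 weeks | Surgery beyond 26 weeks |
|---|---|---|
| 10 | 0.1% | <0.1% |
| 12 | 0.3% | <0.1% |
| 16 | 2.3% | 0.3% |
| 20 | 11.5% | 2.3% |

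**4. Bias if a separate share p of cast patients does not return.** Suppose returners average m weeks and there are no surgical non-attainers. Counting each non-attainer at only 26 weeks, the cast mean is (1 − p)m + 26p. Dropping them gives m. The understatement is therefore at least p(26 − m):

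- p = 0.10, m = 14: 0.10 × 12 = 1.2 weeks (30% of the 4-week target)
- p = 0.20, m = 14: 0.20 × 12 = 2.4 weeks (60%)
- p = 0.20, m = 10: 0.20 × 16 = 3.2 weeks (80%)

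Any surgical non-attainers would offset part of this.

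**5. Power.** If 10%, 20% or 30% of the 21 evaluable cast patients have no value and the difference among the rest stays at 4 weeks, t-test power is 87.5%, 84.2% or 80.0%.

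**6. Simulation.** Lognormal times, SD 5, 84 against 21, cut-off 26 weeks, 4,000 runs per scenario. The t-test uses attainers only; the log-rank test censors the rest. Ranges cover cast means of 10 to 20 weeks with a 4-week difference.

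| Added cast non-attainment | t-test on attainers | Log-rank |
|---|---|---|
| 0% | 89-96% | 76-87% |
| 10% | 86-94% | 92-97% |
| 20% | 83-92% | 98-100% |

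With no added non-attainment, the observed difference is 4.00 weeks at a cast mean of 10, 3.71 at 16 and 3.31 at 20. The skewed tail alone therefore removes some of it when means are long.

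In one further scenario attainers do not differ (mean 10 weeks in both arms) and 20% of cast patients never return. The t-test rejects in 4.7% of runs and the log-rank test in 64.6%.

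**The case against.** The t-test is named for sizing only; Data analysis names no test. An article may leave missing-data rules to the full plan, and inflating N for attrition is routine. All of this is true. That the analysis will compare means is an inference, though a strong one, since it is the only method given for this outcome and mean time is the stated target. If a survival analysis is intended instead, the sizing does not match it. What stands either way is a threshold-crossing time under fixed follow-up that is sized on means.

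Three stronger readings are tempting, and the documents do not support them.

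- **That losses fall mostly in the cast arm.** No section says so. At the single 25% rate, 28 of 35 expected dropouts (80%) are surgical. For non-attainers, a higher cast rate is plausible because the study hypothesises slower return with cast, but it is not documented.
- **That 20% of cast patients will have no value.** The Background does say that "about 20% of fractures fail to heal with conservative treatment". That figure is not specific to the non-displaced mid-third fractures enrolled here, and union is not the PLDL endpoint. The same section puts time to union at 6 to 18 weeks, within follow-up.
- **That the t-test inflates type I error.** About 12% was simulated at 84/21 with SD 4 and 6, but those SDs are invented. With the plan's SD of 5 in both arms the result was 5.1%.

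Primary outcome (2) offers partial cover, since its sizing method accommodates patients who have not returned. It does not repair primary outcome (1).

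**Conclusion.** The point holds in this limited form. Primary outcome (1) is undefined for patients who do not exceed 80% within 6 months or who leave first. The mean-based comparison attached to it would drop them, against the intention-to-treat statement and out of line with the log-rank sizing of primary outcome (2).

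If non-attainment is more frequent with cast, the difference is biased toward zero, which works against the study's own hypothesis. The size depends on a rate the documents do not give. It is negligible if nearly all patients reach 80%: under 3% lie beyond 26 weeks for a normal distribution with SD 5 and a cast mean up to 16 weeks. It is about 1.2 to 3.2 weeks if 10-20% of cast patients do not return and returners average 10-14 weeks, both assumed, with no surgical non-attainers.

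**What to change.** - Analyse PLDL return as censored time to event, with non-attainers censored at last contact or 6 months. An interval-censored model is preferable, because status is known only at contacts and the last gap runs from week 15 to month 6. Alternatively, use adjusted restricted mean time to 26 weeks, which keeps the result in weeks.
- State the assumption about patients who leave early: censoring at last contact treats their loss as uninformative given the covariates.
- Analyse QAS in line with its log-rank sizing, with the rates per follow-up period as description.
- Recheck and restate the power at 112/28 for the chosen method.

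**Cost.** No new data are needed; the planned interviews suffice. The effect measure becomes less simple if a hazard ratio replaces a mean difference. The stated power may also fall below 90%: with no added non-attainment, the log-rank test reached 76-87% at 84/21. That simulation left out the partial follow-up of lost patients, so the recheck should include it.

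### The 92% log-rank power for the second primary outcome is stated for 86 and 30 patients, which matches neither the recommended 112/28, nor the expected 4:1 allocation, nor the 84/21 left after 25% loss

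*Protocol article*

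**What the plan says.** All the figures stand in the Sample size calculation section of the protocol article.

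- **Allocation.** From a survey of clinics, the plan expects that "there will be 1 patient with short arm cast treatment for each group of 4 patients being operated on".
- **Enrolment.** For primary outcome (1), time to the 80% PLDL-wrist threshold, it uses a two-sided t-test at 0.05 with 90% power, a 4-week difference and an SD of 5 weeks. It then writes "As a 25% loss to follow-up is expected", and "we recommend a minimum of 112 patients in the cannulated screw group and 28 patients in the short arm cast group".
- **Primary outcome (2), QAS.** "The sample size calculation for the primary outcome (2) is based on the numbers shown in Table 3". The power statement is conditional: "If the sample size in group A is 86 and the sample size in group 2 is 30". Under that condition, a two-sided log-rank comparison at the 5% level is said to reach about 92% power for the Table 3 curves.

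The section gives no separate enrolment target for outcome (2). It does not say whether 86 and 30 are enrolled or evaluable patients, and it does not relate them to 112 and 28. Under Interventions, Group A is the operative group. I read "group 2" as Group B, the cast group.

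**The concern.** A trial has one enrolment, so both primary outcomes should be powered at the same numbers. Here the second is powered on a cast arm of 30, while the recommended minimum is 28 before loss and 21 after it. The cast arm is the small one and limits the precision of the comparison. The split of 86 to 30 also departs from the 4:1 ratio on which the enrolment rests.

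The QAS result is one of two declared primary outcomes. If it is not significant, readers will judge it against a stated type II error of about 8%. The plan does not show that its own enrolment supports that figure.

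**Working it through.** **1. Reproduce the enrolment for outcome (1).** Inputs: difference 4, SD 5, two-sided alpha 0.05, power 90%, ratio 4:1.

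- Cast arm: (1 + 1/4) × (1.960 + 1.282)² × 5²/4² = 1.25 × 10.51 × 1.5625 = 20.5, rounded up to 21. Operative arm: 4 × 21 = 84.
- Exact t-test power at 84/21 is 90.1%.
- With 25% loss: 84/0.75 = 112 and 21/0.75 = 28.

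The plan's figures reproduce exactly. So 112/28 is the loss-inflated form of 84/21.

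**2. Set the two calculations side by side.**

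| | Operative | Cast | Ratio | n₁n₂/(n₁+n₂) |
|---|---|---|---|---|
| Log-rank statement | 86 | 30 | 2.87:1 | 22.24 |
| Recommended enrolment | 112 | 28 | 4:1 | 22.40 |
| After 25% loss | 84 | 21 | 4:1 | 16.80 |

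The operative arm after loss is practically met (84 against 86). The shortfall is in the cast arm: 28 against 30 before loss, and 21 against 30 (30% fewer) after it.

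**3. Rescale the stated power.** The Table 3 curves are not in the text at hand, so the 92% cannot be rebuilt and is taken as given. For fixed curves and a fixed event fraction, the expected log-rank statistic is proportional to √[n₁n₂/(n₁+n₂)]. At 92% power it is 1.960 + 1.405 = 3.365.

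- **84/21, lost patients contribute nothing:** 3.365 × √(16.80/22.24) = 3.365 × 0.869 = 2.925. Then 2.925 − 1.960 = 0.965, so power is 83.3%. If "approximately" covers 91.5% to 92.5%, the result is 82.5% to 84.0%.
- **112/28, no loss:** 3.365 × √(22.40/22.24) − 1.960 = 1.417, so power is 92.2%.

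**4. Allow for gradual censoring.** A patient lost part-way counts in a log-rank test until censored. The following was simulated with assumed exponential times, 26 weeks of follow-up, 25% lost at times uniform over 26 weeks, and 4,000 runs per cell. The rows shown are those in which 86/30 without loss falls closest to 92%.

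| Cast median (weeks), hazard ratio | 86/30, no loss | 112/28, 25% gradual loss | 84/21, complete |
|---|---|---|---|
| 8, 2.1 | 91.1% | 88.8% | 82.6% |
| 8, 2.2 | 93.4% | 92.0% | 86.5% |
| 12, 2.2 | 92.5% | 90.8% | 83.5% |

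Gradual loss at 112/28 costs about 1 to 3 points against 86/30 without loss. A variant in which events are seen only at the scheduled contacts gave 88–91%. The medians, hazard ratios and loss pattern are assumptions, not figures from the plan.

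**5. What holding 92% would take if lost patients contribute nothing.** At the 86:30 split: 86/0.75 = 114.7 and 30/0.75 = 40, so 115/40 (155 in total, against 140). At 4:1, the evaluable cast arm is 22.24 × 5/4 = 27.8, and 27.8/0.75 = 37.1, so 38 cast and, by the same route, 149 operative. This shows the size of the gap; it is not a recommendation.

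**The case against.** The power sentence is conditional and never claims 92% at 112/28. No printed number is shown to be wrong: outcome (1) reproduces, and the 92% cannot be tested without Table 3. The enrolment is also called a minimum. All of this stands, and it makes the fault an unreconciled pair of inputs rather than a wrong calculation. It does not remove the fault, because the sentence is the only power statement for a primary outcome and its condition is not the planned enrolment.

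Three stronger readings are tempting, and the document does not support them.

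- **That power simply is about 83%, so that the type II error doubles from 8% to 17%.** This requires every lost patient to contribute nothing. That suits a t-test on a time that is either obtained or not, as in outcome (1). It is the extreme case for a log-rank test with contacts planned at 3, 6, 9 and 15 weeks and at 3 and 6 months. With gradual loss the type II error is roughly 9–12%.
- **That 86 and 30 carry no loss allowance.** The text does not say so, and the Table 3 inputs cannot be seen. If they are enrolled numbers with loss already built in, 112/28 gives about 92%. Even then 86/30 differs from the recommended enrolment and from 4:1, so the paragraph still needs reconciling.
- **That the trial is underpowered and must grow.** Even the lower bound exceeds 80%.

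**Conclusion.** The inconsistency is firm and needs neither Table 3 nor any distributional assumption: 86/30 conflicts with 112/28, with 84/21 and with 4:1, and the cast arm is below 30 with or without loss.

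The effect on power is a range. With the 92% accepted as correct, power at the recommended enrolment is about 83% if lost patients give no data, and roughly 88–91% if they are censored gradually under the assumptions above. It is near 92% only with no loss, or if loss is already in the Table 3 inputs. The severity is moderate: a stated power that the enrolment does not support as written, not a failure of the design.

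**What to change.** In the Sample size calculation section:

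1. State whether 86 and 30 are enrolled or evaluable patients, and whether the Table 3 inputs already allow for loss.
2. Recompute the log-rank power from the Table 3 curves at 112/28 enrolled (4:1), with the 25% loss as an explicit censoring assumption.
3. Replace the 92% at 86/30 with that figure, and give about 83% as the lower bound for the case in which lost patients contribute no data.

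The 83% should not be printed as the power itself, since it is a rescaling made without sight of Table 3. The cost is one recalculation and one rewritten paragraph. No extra patients and no change to design, endpoints or analysis are needed. The downside for the sponsor is that the stated power will probably be less favourable.

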**Methods/Design:**

The study is designed as a non-randomized multiple center cohort study including 12 sites in Germany and Austria. The inclusion period is planned to be 12 months with a follow up of 6 months. Allocation to operative or non-operative treatment is choosen by the patient together with his treating surgeon. The primary outcome is time to return to previous activity level adapted for loading of the wrist in daily life as measured by a newly developed questionnaire (PLDL-wrist). Factors identified a priori to be associated with the outcome, e.g., poverty status, age, education, smoking status, gender, and occupation, are measured to ensure adequate control for their potential confounding effects.

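### The abstract names one primary outcome and the body two, each sized at the full two-sided 0.05 under a single null tied to neither, so a 5% type I error is not guaranteed

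*Protocol article*

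**What the plan says.** All references are to the protocol article.

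- **Abstract, Methods/Design.** One primary outcome, measured by the PLDL-wrist questionnaire: "The primary outcome is time to return to previous activity level adapted for loading of the wrist in daily life".
- **Primary outcome measures.** Two numbered outcomes. (1) is the time until the PLDL-wrist score reaches 80% of the patient's own baseline. (2) is QAS status: a return to full work plus full household duties, or to household duties alone for those without a job. Each is presented as the point at which the patient is back at the earlier activity level.
- **Data analysis.** Again counts two primary outcomes. The only rule stated for them is analysis by intention to treat.
- **Hypothesis and Null hypothesis.** One of each. The null begins "There will be no difference in terms of return to previous activity level" and does not say which instrument decides it.
- **Sample size calculation.** The calculation for outcome (1) "is based on a two-sided two-sample t-test, a significance level of 0.05 and a power of 90" per cent. Outcome (2) is powered at approximately 92% using "the log-rank test for equality of survival curves with a 0.050 two-sided significance level".

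**The concern.** The number of primary outcomes differs between the abstract and the body. The phrase on which the single null rests has two operational definitions, and each has its own test at the full 0.05. A reader cannot tell from the article which result, or which combination of results, rejects the null.

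The answer changes the operating characteristics. If either test suffices, there are two chances of a false positive and the error exceeds 5%. If both are needed, neither 90% nor 92% is the power of the study. If only PLDL-wrist counts, as the abstract says, both the 5% and the 90% stand, but QAS is then not primary. If one outcome is significant and the other is not, the article does not settle in advance how the hypothesis is to be judged.

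**Working it through.** **Step 1. Reproduce the stated sample size for outcome (1).** All inputs are from Sample size calculation:
- effect and spread: "A difference of 4 weeks between the two groups is likely and a standard deviation of 5 weeks is anticipated"
- allocation: "the odds of patients receiving non operative treatment in relation to those receiving surgery is 1:4"
- attrition: "As a 25% loss to follow-up is expected"
- two-sided 0.05, power 90%

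With four operated patients per cast patient, the cast group needs

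n = (1 + 1/4) × (1.960 + 1.282)² × 5² / 4² = 20.5, rounded up to 21.

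The operative group is 4 × 21 = 84. Dividing by 0.75 gives 28 and 112, which matches the article: "we recommend a minimum of 112 patients in the cannulated screw group and 28 patients in the short arm cast group". An exact noncentral-t check at 21 and 84 gives power 0.901. The stated figure therefore uses the whole 0.05 for outcome (1) and reserves nothing for a second primary test.

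The 92% for outcome (2) is taken as stated. It rests on Table 3, which is not in the text available, so it was not reproduced.

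**Step 2. Type I error if either test may reject the null.** For independent tests: 1 − 0.95² = 0.0975. For correlated tests: 1 − P(|Z1| < 1.96 and |Z2| < 1.96) under a bivariate normal. The correlation is an assumption.

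| Assumed correlation | Error, either counts |
|---|---|
| 0 | 9.75% |
| 0.5 | 9.1% |
| 0.7 | 8.4% (0.0835) |
| 0.8 | 7.8% |
| 0.9 | 7.0% |
| 1 | 5.0% |

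Whatever the correlation, the error cannot exceed 0.05 + 0.05 = 10%.

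**Step 3. Both tests required.** The type I error is then at most 5%. If there is no effect on either outcome, it is 0.25% at correlation 0 (0.05²) and 3.0% at 0.9. Joint power on the stated figures is 0.90 × 0.92 = 0.828 at correlation 0. From the bivariate normal it is 0.848 at 0.5 and 0.880 at 0.9.

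**Step 4. An alpha split, for comparison.** At 0.025 each, outcome (1) needs 25 cast and 100 operated evaluable patients. After dividing by 0.75 this is 34 + 134 = 168, against the planned 112 + 28 = 140. If 21 and 84 evaluable are kept, the power of the t-test falls from 0.901 to 0.841. The stated 92% for the log-rank test would fall to about 87%.

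**Step 5. One primary outcome, then a fixed order.** PLDL-wrist keeps 0.05, so the calculation in Step 1 is unchanged. QAS is tested only after PLDL-wrist has been rejected, so the error across both stays at or below 5%.

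**The case against.** **The rule may be elsewhere.** This is a condensed journal article, and test order or decision rules are often left to the full protocol or analysis plan. That stands: the absence of a multiplicity rule is not the point here. What remains is on the page: one primary outcome against two, one null with two definitions, and both outcomes sized at full alpha. A rule written elsewhere would also have to fit that sizing, and an alpha split would not (Step 4).

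**A stronger reading.** A reader might infer that the 5% error rate fails outright. The documents do not support that, because they never commit to an either-counts rule. The 5% holds under a single primary outcome, which is the literal reading of the abstract, and also under a fixed order or a both-required rule.

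**Independence is unlikely.** Both outcomes measure return to activity in the same patients on the same follow-up schedule, so 9.75% is at the upper end. This is fair, and the range should be read as assumed. At correlation 0.9 the error is still 7.0%.

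**Other threats are larger.** The study is not randomized, and adjustment for confounders is placed in the secondary analysis. An excess of 2 to 5 percentage points may not be the main source of a false conclusion. That limits the practical weight of the point. But the article sets a formal null, alpha and power, and those need one decision rule.

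**Discordant results could be reported side by side.** True, and the data would still inform. It would not settle whether the stated null is rejected.

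**Conclusion.** The point holds in a limited form. The article contradicts itself on how many primary outcomes there are, and it sizes both at two-sided 0.05 under one null assigned to neither. Control of the type I error at 5% is therefore not guaranteed, which is less than saying that it is lost.

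The size depends on the rule that is meant: an error of about 7.0% to 9.75% if either outcome counts, or a joint power of about 83% to 88% if both are required. Both ranges assume a bivariate normal with correlation between 0 and 0.9. The second also takes the stated 90% and 92% at face value, although they refer to different patient numbers: 84 and 21 evaluable for outcome (1), 86 and 30 for outcome (2). Whether the 92% applies to the planned sample is a separate question and is not used here.

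This should be corrected. It does not invalidate the sample size for outcome (1).

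**What to change.** Preferred change, following the abstract:

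1. Name time to the individual 80% PLDL-wrist threshold as the single primary outcome, tested at two-sided 0.05.
2. Make QAS the key secondary outcome, tested at two-sided 0.05 only if the PLDL-wrist test is significant.
3. State in Hypothesis and Null hypothesis that they refer to the PLDL-wrist endpoint, and bring Primary outcome measures, Sample size calculation and Data analysis into line.

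The cost is wording only. The 112 + 28 patients for PLDL-wrist are unchanged. The downside is that QAS loses stand-alone primary status. Its chance of being declared significant in this order is the joint figure of about 83% to 88% rather than 92%, on the same assumptions. This matters because the article gives QAS a purpose of its own: covering patients without formal employment.

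The choice is the sponsor's. If both are to remain primary, the article should say that both must be significant and replace the separate 90% and 92% with the joint power, stating the correlation assumed.
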